#### Strategies for trial retention

During weekends, participants allocated to both groups receive phone calls to reinforce intervention session time and place. We use phone calls to inquire about any adverse events if a participant misses a session of any intervention arm. The phone call schedule will cease for participants declaring their withdrawal from the study.

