### Intervention

The participants are randomly allocated to a functional training program or a strength training program, each lasting 3 months. The exercise sessions are completed at the Center of Clinical Research at the HCPA. The patients perform the exercise training three times/week for a total of 36 sessions. Both physical exercise training programs are performed under the supervision of a physiotherapist who specialized in sports sciences. The exercises are performed individually or in pairs. Resting heart rate (HR) and blood pressure are measured with a validated digital automatic sphygmomanometer before and after each training session. The first two training sessions are earmarked for patients to become familiar with the exercises.

Each training session lasts approximately 50–60 min, consisting of an initial warm-up of 5 min, 35–45 min of functional or strength exercises, and 10 min of stretching and cool-down (Table 1).

**Table 1 Tab1:** Phases of the sections and collection of exercises performed in training protocols

Functional Training Session	Strength Training Session	Time
***Warm-up:*** Run on the trampoline	***Warm-up:*** Stationary gait and calisthenics exercises	5 min
***Functional exercises:*** Core strength Agility and balance Knee and hip dominance Vertical pressure Horizontal pressure Horizontal and vertical pulling	***Strength exercises:*** Shoulder abduction Triceps extension Biceps curls, bench press Abdominals, calf raises Leg extension, seated leg curl Leg press and leg abduction	35–45 min
***Cool-down:*** Stretching exercises for lower limbs, upper limbs, and spine	***Cool-down:*** Stretching exercises for lower limbs, upper limbs, and spine	10 min

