#### Harms

The study will monitor for the following physical training-related adverse effects during the intervention period: shortness of breath, fatigue, and muscular pain. The researcher responsible for the intervention will identify possible solutions for any adverse effects.

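### The stated breadth of adverse-event enquiry depends on attendance; one identical open question in the weekend call would even it out at almost no cost

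*Protocol article*

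**What the plan says.** Two sections of the protocol article describe how harms come to light.

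- **Strategies for trial retention.** The open enquiry is triggered by absence: "We use phone calls to inquire about any adverse events if a participant misses a session of any intervention arm". The call that everyone gets has another purpose: "During weekends, participants allocated to both groups receive phone calls to reinforce intervention session time and place". On leaving: "The phone call schedule will cease for participants declaring their withdrawal from the study".
- **Harms.** "The study will monitor for the following physical training-related adverse effects during the intervention period: shortness of breath, fatigue, and muscular pain". On handling them: "The researcher responsible for the intervention will identify possible solutions for any adverse effects".

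Three other places matter:

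- **Intervention** sets the in-person contact, the same in both arms: "The patients perform the exercise training three times/week for a total of 36 sessions", and "Both physical exercise training programs are performed under the supervision of a physiotherapist who specialized in sports sciences". Heart rate and blood pressure are taken before and after each session.
- **Criteria for discontinuation and safety interventions** lists symptoms that interrupt a session. For any participant, it makes a cardiovascular event, a hospital admission or a severe health event a reason to discontinue.
- **Background**, last paragraph, gives the safety of the functional programme as the third secondary objective. It is worded without a comparison, unlike the first secondary objective.

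**The concern.** The two sections differ in what is asked and of whom. The missed-session call is open to any event. The Harms section is limited to three symptoms presumed to come from training. Followed as written, the breadth of the question is set by whether the participant turned up.

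The gap concerns attenders. The functional programme includes trampoline running, a balance board, agility work on a ladder and Swiss-ball exercises. A fall, a joint injury or an illness at home is not among the three symptoms. Neither the supervision nor the vital-sign checks amount to a stated question about events since the last session. If such events are undercounted, the third secondary objective is answered too favourably, and that would be so even if safety were described in the functional arm alone.

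Attendance is also measured after randomisation, and the article treats adherence to both programmes as an outcome. If attendance differs between arms, the mix of narrow and open enquiry differs too.

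**Working it through.** The article states no adverse-event rate, no detection probability and no attendance by arm, so there is no planned figure to reproduce. The check has three steps.

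**1. Stated enquiry, side by side**

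| Situation | Stated contact | Stated scope |
|---|---|---|
| Session attended | Supervised session, vital signs before and after | Three named symptoms (Harms), plus in-session warning symptoms |
| Session missed | Phone call | Any adverse event |
| Weekend, both arms | Phone call | Session time and place |
| After declared withdrawal | Calls end | None by this route |

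**2. Number of contacts.** The article gives 36 sessions. Assuming one call per missed session, attended sessions plus missed-session calls always total 36:

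- 10% missed: 32.4 + 3.6 = 36
- 25% missed: 27 + 9 = 36
- at the 80% adherence line: 0.80 × 36 = 28.8, so at least 29 attended and at most 7 missed, and 29 + 7 = 36

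The number of contacts therefore does not depend on attendance. Only their mode and scope do.

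**3. What uneven scope could do (illustration, all values assumed).** Let *a* be attendance, *s1* the chance that an event is picked up at an attended session, and *s2* the chance that it is picked up by the missed-session call. The fraction detected in an arm is

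D = a × s1 + (1 − a) × s2

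With equal true event rates, the between-arm detection ratio is D(arm 1) / D(arm 2).

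| s1 / s2 | 80% v 80% | 90% v 70% | 95% v 60% |
|---|---|---|---|
| 0.9 / 0.9 | 1.00 | 1.00 | 1.00 |
| 0.9 / 0.6 | 1.00 | 0.87/0.81 = 1.07 | 0.885/0.78 = 1.13 |
| 0.9 / 0.3 | 1.00 | 0.84/0.72 = 1.17 | 0.87/0.66 = 1.32 |
| 0.6 / 0.9 | 1.00 | 0.63/0.69 = 0.91 | 0.615/0.72 = 0.85 |
| 0.3 / 0.9 | 1.00 | 0.36/0.48 = 0.75 | 0.33/0.54 = 0.61 |

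The last row is closest to the scope gap for events outside the three symptoms, with a narrow in-person enquiry and an open phone question. There, equal attendance of 80% leaves the ratio at 1.00, but each arm detects only 0.80 × 0.3 + 0.20 × 0.9 = 0.42 of events. Undercounting can thus occur with no distortion between arms.

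For withdrawal at mid-period in fractions w1 and w2, the ratio of observed time is (1 − w1/2) / (1 − w2/2). This is 1.00 at 20% v 20%, and 0.95/0.85 = 1.12 at 10% v 30%. The article plans for 20% loss or refusal overall and gives no split by arm.

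**The case against.** The strongest reply is that the retention section is not the harms plan. The Harms section monitors throughout the intervention period without an attendance condition, a physiotherapist sees attenders three times a week, and the discontinuation criteria cover serious events in any participant. On this view the missed-session call replaces a lost contact. All of that stands, and it rules out four stronger readings that a reader might take from the text.

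- **That harm detection rests on attendance alone.** It does not, because an attender has up to 36 supervised contacts.
- **That the arms' safety results cannot be compared.** The rule is identical in both arms. Distortion through attendance needs attendance to differ between arms and the two routes to detect differently, and the article gives no sign of either. It also states no between-arm safety test.
- **That the arm with poorer attendance must show more events.** The table runs both ways. If supervision detects better than a call, that arm shows fewer. Counting calls alone, for instance 9 against 3.6 (2.5-fold) at assumed absence rates of 25% and 10%, leaves out the sessions and does not measure bias.
- **That ending calls at withdrawal is an error.** The text concerns people who declare that they are leaving the study. It does not say that calls end for someone who only stops training, or that the reason for leaving goes unasked.

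It is also fair to say that this is a condensed article and that session-level questions may sit in a fuller protocol or operating procedure. The absence of such detail is therefore not the point. The point is that the two scopes the article does state are different and should be reconciled.

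**Conclusion.** The point holds as a cheap improvement. As stated, the enquiry is open for absentees and limited to three symptoms for attenders, and the one call that reaches everyone is not used to ask about harms. Events outside the three symptoms, or between sessions, may be undercounted for the third secondary objective. Ascertainment could differ between arms, in either direction, if attendance differs.

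The size cannot be fixed from the article. On the assumed values it is nil at equal attendance, 0.75 to 1.17 at 90% v 70%, and 0.61 to 1.32 at 95% v 60%. This rests on reading the Harms list as the scope applied at sessions. If attenders are in fact asked an open question at each session, the scope gap closes and only the wording needs aligning. With 19 planned per arm, a few unrecorded events could still change the safety description.

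**What to change.** Reconcile the retention and Harms sections so that one question, worded identically, is put to everyone:

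- Add an open question about any new health event since the last contact to the weekend call in both arms. Assuming one call per weekend, that is 12 uniform enquiries per participant over 12 weeks.
- Record every answer, whatever the attendance and whatever the presumed cause. Keep the three symptoms as a prompted list within the same record.
- Keep the missed-session call as an extra contact, and mark which events came from which route.
- At declared withdrawal, ask whether an event was the reason. Continue the question to week 12 only for those who agree to be contacted.
- Base any safety description by arm on the scheduled enquiries, and keep the answers from the outcome assessors, in line with the article's masking arrangement.

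No training content, schedule or clinical rule changes. The cost is perhaps a minute (assumed) on calls already made, 12 × 38 = 456 over the whole trial at the planned enrolment, plus a short amendment to the protocol and operating procedure. There will be more minor events to log. Participants already treated have only the old collection, so the report must state the date of the change and show safety data before and after it separately.

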### Outcomes

The outcomes are assessed at baseline and after the provision of written informed consent but before allocation to one of the study groups. At the end of the 12-week period, the subject will be re-evaluated (Fig. 2).

**Fig. 2 Fig2:**
[figure not shown]
Proposed trial design

Patients’ baseline demographic and clinical information including age, sex, HF etiology, left ventricle ejection fraction, and NYHA functional class are obtained from their electronic health records.

The primary outcome measures are cardiopulmonary exercise capacity and quality of life; the secondary outcomes include assessment of functionality, peripheral and inspiratory muscle strength, endothelial function, lean body mass, and participant adherence to exercise programs.

### Measurement of primary outcomes

#### Cardiopulmonary exercise capacity

Cardiopulmonary exercise testing with expired gas analysis is performed on a treadmill (T2100, General Electric, WI, USA; speed 0–22 km/h [0–13.5 mph], grade 0–26%). A ramp protocol is used with a starting speed of 2.0 km/h or 2.5 km/h and a starting grade of 0%. Increments of 0.5 km/h per minute in speed and 1% per minute in grade were used to achieve fatigue within 8–12 min. During the test, gas exchanges are continuously measured breath-by-breath by a previously validated system (Quark CPET; COSMED, Rome, Italy).

Blood pressure is monitored every 3 min using a sphygmomanometer. HR is monitored using 12-lead electrocardiography (Quark C12x; COSMED) with electrode placement as described by Mason and Likar [22]. The test analyzes the ventilatory and metabolic variables. Peak VO_2_ is set to the highest 20-s average value reached during the test. Maximality criteria are defined by a respiratory exchange ratio greater than or equal to 1.05.

#### Quality of life

The Minnesota Living with Heart Failure Questionnaire, a disease-specific instrument used to assess quality of life, consists of 21 questions about limitations that are often associated with how HF prevents patients from living as they would like to. Patients answer the questions as they related to the previous month. The total score is 0–105 points. A low score reflects a better health-related quality of life. The instrument is validated in Portuguese [23].

### Measurement of secondary outcomes

#### Functionality

The Duke Activity Status Index is a 12-item questionnaire that assesses daily activities. Each item has a specific weight based on metabolic equivalents. The participants identify each of the activities that they can perform. The final score is 0–58.2 points. A higher score represents better functional capacity. The instrument is validated in Portuguese [24].

The gait speed test is used to evaluate and monitor the functional status and general health of a wide variety of populations. The method requires a 20-m corridor. The patient walks at his own pace, without running, and the time spent in the central 10 m of the corridor is determined. The ratio between distance and time (meters/second) will then be calculated [25].

#### Peripheral muscle strength

The hand grip dynamometer has been widely used to evaluate the nutritional status, functional, lateral dominance, and total strength of individuals always divided into groups by sex and age. Hand grip strength is assessed as recommended American Association of Hand Therapists [26] using a JAMAR® dynamometer (Sammons Preston, Inc., Bolingbook, IL, USA). The strength values in kilograms ​​will be calculated as the average of three attempts for the dominant hand performed at 1-min intervals between measurements.

#### Inspiratory muscle strength

Manovacuometry assesses inspiratory muscle strength or maximal inspiratory pressure (MIP) by maintaining a maximum negative pressure for at least 1 s after a forced expiration to residual volume against an occluded airway as recommended by the American Thoracic Society. At least three reproducible maneuvers must be performed using a digital pressure manometer (MVD300; Globalmed, Porto Alegre, Brazil). For the data analysis, the highest value is recorded if it does not exceed the second highest value by 10% [27].

#### Endothelial function

Noninvasive measurements of endothelial function are obtained by flow-mediated dilation of the brachial artery using two-dimensional ultrasonography. Its measurement is performed in accordance with published guidelines [28] always by the same trained operator ([name]). Briefly, the examination starts after a 15-min rest in a temperature-controlled room with the patient supine and the arms in a comfortable position. Any vasodilators are discontinued at least 4 h before the examination if possible. The individuals are advised to refrain from exercising, drinking caffeine, and smoking for at least 4 h before the examination.

#### Lean body mass

The arm muscle circumference is obtained from arm circumference and tricipital skinfold measurement using a tape measure and an adipometer, respectively [29].

#### Adherence

Adherence to an exercise program has been classified as meeting at least 80% of the recommended or prescribe exercise dose. Any participant who demonstrates a training protocol adherence of 80% or more than 36 sessions will be considered adherent. Participants will be classified as non-adherent or partially adherent if their adherence is less than 80% [30].

### Sample size

Our sample size calculation was based on Feiereisen et al., who enrolled subjects with HF with reduced ejection fraction to assess the effect of strength in comparison with aerobic and combined aerobic-strength training on their peak VO_2_ [31]. Considering a power of 80%, a significance level of 5% and an effect size of 0.2 for the peak VO_2_, a total sample size of 32 subjects was estimated, including 16 in each study group. To account for a 20% estimated participant loss or refusal rate, we defined that 19 patients should be enrolled in each group, totalizing 38 subjects.

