## Methods/design

### Study setting

This randomized parallel-design 1:1 ratio allocation examiner-blinded clinical trial is conducted at the Hospital de Clínicas de Porto Alegre (HCPA), a tertiary hospital in the city of Porto Alegre, Southern Brazil. The study was approved by the facility’s institutional review board on August 8, 2017 (protocol no. 20170291). The study protocol adheres to the SPIRIT 2013 recommendations [19] (Additional file 1). The World Health Organization Trial Registration Dataset is provided herein (Additional file 2). Written informed consent is obtained from all patients before participation (Additional file 3).

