### Statistical analysis

The characterization of the sample will be performed by descriptive statistical analysis using measures of central tendency (mean and median) and variability (standard deviation and interquartile range). The normality of the data will be tested by the Shapiro-Wilk test. Intra- and inter-group analyses will be performed before and after the total 12-week intervention period. For both analyses the generalized estimation equations (GEE) will be used. Correlations between peak VO_2_ and study variables – quality of life, functionality, muscle strength, endothelial function, and lean body mass – will be examined by Pearson or Spearman coefficients as appropriate.

In all tests, a significance level of *p* < 0.05 will be adopted. All data will be analyzed using SPSS Statistics for Windows version 20.0 (IBM Corp., Armonk, NY, USA) by the intention-to-treat and protocol methods.

Dropouts (essentially, participants who withdraw consent for continued follow-up) or missing data will be included in the analysis by modern imputation methods.

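### Enrolling 38 does not cover the stated 20% loss: it keeps the required 32 only if loss after enrolment is at most 15.8% (minor)

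*Protocol article*

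**What the plan says.** The Sample size section gives three linked figures.

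- Requirement: "a total sample size of 32 subjects was estimated, including 16 in each study group".
- Allowance and enrolment target, in one sentence: "20% estimated participant loss or refusal rate, we defined that 19 patients should be enrolled in each group, totalizing 38 subjects".

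The requirement is said to follow from these inputs: "Considering a power of 80%, a significance level of 5% and an effect size of 0.2 for the peak VO_2". The section states neither the metric of that effect size nor the formula used for the allowance.

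Two other sections bear on the point. Recruitment describes patients being invited first, with only those who accept being tested and then allocated. Statistical analysis says how losses are to be handled: "Dropouts (essentially, participants who withdraw consent for continued follow-up) or missing data will be included in the analysis by modern imputation methods".

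**The concern.** An allowance for loss should leave the required number after the loss has occurred, so the requirement is divided by the fraction expected to remain. The target of 19 per group looks instead like the requirement multiplied by 1.2 and rounded down. Multiplying gives too small a figure, and rounding down makes it smaller still.

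If so, the trial would finish below its own required number under its own loss assumption, and the stated 80% power would not be reached even if every other input were right. The allowance also combines refusal with loss. Someone who declines before allocation takes no place in either group, so only loss after randomisation should enter the calculation.

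**Working it through.** **Inputs, all from the Sample size section:** 16 per group (32 in total) required; 20% loss or refusal; 19 per group (38 in total) enrolled. Allocation is 1:1 (Study setting).

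**1. Where 19 and 38 appear to come from.** Required number × (1 + loss):
- per group: 16 × 1.20 = 19.2, rounded down to 19
- total: 32 × 1.20 = 38.4, rounded down to 38

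This reproduces the stated target. The route is an inference, since no formula is given, but steps 2 to 4 do not depend on it.

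**2. What 38 leaves at 20% loss.** Enrolled × (1 − loss):
- per group: 19 × 0.80 = 15.2, against 16
- total: 38 × 0.80 = 30.4, against 32

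**3. The loss that 38 can absorb.** (Enrolled − required) / enrolled:
- per group: (19 − 16)/19 = 3/19 = 15.8%
- total: (38 − 32)/38 = 6/38 = 15.8%

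**4. The enrolment that covers 20%.** Required number / (1 − loss):
- per group: 16/0.80 = 20
- total: 32/0.80 = 40
- check: 20 × 0.80 = 16

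The target is one patient per group, two in total, too low.

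**5. Effect on power, conditional on the plan's premise.** The stated 0.2 cannot be used directly because its metric is not given. So take the plan at its word that 16 per group gives 80% power and ask what a smaller number gives. Two models were tried; neither is stated in the article.

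| Model (assumed) | At the required number | At about 20% loss |
|---|---|---|
| Two-sided 5% t-test, standardised difference solved so that 16 per group gives 80% (1.024) | 80.0% at 16 per group | 77.8% at 15.2 per group; 77.2% at 15 |
| Group-by-time interaction F test, Cohen's f = 0.2, pre-post correlation 0.7 | 80.7% at 32 in total | 77.9% at 30 in total |

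The drop is 2 to 3 percentage points in both.

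**6. Chance of ending with at least 32 completers if each patient has an independent 20% risk of loss (binomial).**
- 38 enrolled: 34%
- 40 enrolled: 59%

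The second figure is the benchmark for the first. Even the correct inflation meets the target only on average.

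**The case against.** **The gap is trivial.** It is 0.8 of a patient per group, and the 20% is itself an estimate. The difference between 15.8% and 20% lies well within what anyone could predict for a single-centre trial of this size. This stands, and it is why the point is minor. It does not make the three figures agree.

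**Part of the 20% may be refusal.** If enough of it is refusal before enrolment, loss among the 38 could be 15.8% or less and the target would suffice. This stands as a condition. The article gives no split, yet it applies the whole allowance to the number enrolled, while its Recruitment section places refusal before allocation. The sentence needs correcting either way.

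**Dropouts will be imputed.** They stay in the analysis set, and their baseline data can contribute, so a completers-only t-test is not the planned generalised estimating equations analysis. That is a fair limit on the power figures. But outcomes are measured only at baseline and study completion, and imputation does not restore a 12-week value that was never observed.

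**A stronger reading to avoid.** A reader might infer that power for the stated planning effect falls to 77%. The documents do not support that. The standardised difference of 1.024 was solved backwards from 80% power at 16 per group and appears nowhere in the article. If 0.2 were a standardised mean difference, power at 16 per group would be only about 8.5%, and the requirement of 32 would not follow at all. That is a separate question. Likewise, the 34% in step 6 quoted without its 59% benchmark would make a two-patient gap look larger than it is.

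**Conclusion.** The point holds as a minor arithmetic error. On the article's own figures, 38 does not deliver a 20% allowance: it delivers 15.8%, and the figure for 20% is 40. The shortfall is two patients at enrolment, or 32 − 30.4 = 1.6 patients with outcomes.

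It rests on one assumption, that the full 20% is lost after enrolment. The consequence for power, roughly 77–78% in place of 80%, rests on a second: that 16 per group really gives 80%. The article asserts this, but it cannot be confirmed from the stated effect size. Nothing here threatens the validity of the comparison between the groups.

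**What to change.** Restate the last sentence of the Sample size section so that the target and the allowance agree. Either form would do:

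- 38 patients will be enrolled, which allows for about 16% loss after randomisation; or
- 38 patients will be enrolled, leaving about 30 with outcomes at 20% loss, slightly below the 32 required.

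In both, apply the allowance to loss after randomisation only and drop refusal from it. Do not print 77% as the power for the stated effect size, since the stated inputs do not yield that figure.

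The cost is one sentence and a slightly less favourable stated figure. If the sponsor prefers to keep the 20% allowance as stated, the matching target is 40 (20 per group), which costs two more patients.
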